### Outcomes

Assessment of outcomes will require follow-up by individual healthcare professionals, by accessing medical records routinely available to them as part of the clinical care team. When a pregnant woman with SARs-CoV-2 infection or suspected COVID-19 is registered on the database, they will automatically be assigned a unique participant identification number. Date of birth and NHS number, or equivalent in non-UK centres, will be stored on the database. The limit for data collection will be 28 days after the delivery or pregnancy loss of the last woman registered. Linkage will allow data up to 2 years of age to be collected for preterm babies in the UK with the NNRD database.

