## Methods and analysis

This is an observational global pregnancy and neonatal register (PAN-COVID registry) collecting outcome data from women in pregnancy who have confirmed SARS-CoV-2 infection or signs and symptoms of COVID-19 during their pregnancy. The study is sponsored by Imperial College London and funded by UK Research Institute and National Institute of Health and Research (NIHR). The study received Urgent Public Health (UPH) prioritisation in the UK in April 2020.

The main study objectives are, first, to establish a UK and international disease registry for women with suspected COVID-19 or confirmed SARS-CoV-2 infection in pregnancy; in the UK, this will be linked to neonatal data (from NNRD). Second, PAN-COVID investigators aim to publish regular reports focused on our principle research question: in women recruited to the PAN-COVID registry with suspected or confirmed SARS-CoV-2 infection, what is the incidence of (a) miscarriage, (b) small for gestational age (SGA)/FGR and stillbirth, (c) preterm birth and (d) suspected or confirmed vertical transmission to the neonate and perinatal infection.

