### Data entry

Demographics—date of birth, National Health Service (NHS) number (or international equivalent), smoking status, last menstrual period, expected date of delivery, body mass index, history of previous pregnancies/miscarriages/loss/small for gestational age/delivery (preterm/term), comorbidities, medications, ethnicity, number of fetuses, structural abnormality on ultrasound.

COVID-19 signs and symptoms—fever, new persistent cough, anosmia, myalgia, diarrhoea, shortness of breath, fatigue, abdominal pain, chest pain, hoarseness of voice, loss of appetite, delirium.

SARS-CoV-2 infection—SARS-CoV 2 test performed, date of test(s), results of test(s) (if available)

COVID-19 treatment—requirement for (including duration of) inpatient, level 2 or 3 critical care, supplementary oxygen, non-invasive ventilation, endotracheal intubation, extracorporeal membrane oxygenation, antiviral/other specific anti-COVID-19 therapy, iatrogenic delivery or termination due to maternal compromised from COVID-19.

Maternal outcomes—non-invasive ventilation, intubation and ventilation and maternal death.

Comorbidities—hypertension, respiratory disease, cardiovascular disease, renal disease, autoimmune disease, medications including aspirin, progesterone, others.

Delivery details—iatrogenic/spontaneous, date of delivery/miscarriage, mode of delivery, live birth/stillbirth/miscarriage, birth weight, sex.

Postnatal outcomes—breastfeeding, baby cared for separately from mother until discharge.

Neonatal outcomes—date of birth, birth weight, gestation at birth, Apgar at 5 min, neonatal death, COVID-19 transmission (neonate with positive swab/serology), congenital abnormality/deformation, date of discharge from hospital, readmission up to 28 days of life.

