### Study population

Study centres will be asked to identify eligible women of childbearing age (18–50 years) at the time of an early pregnancy attendance or at delivery who have had suspected COVID-19 or confirmed SARS-CoV-2 infection in pregnancy. Case data will be entered into the online registry. The study will recruit women affected by suspected COVID-19 or confirmed SARS-CoV-2 infection from January 2020 and March 2021. Participants will be able to withdraw from the register at any time without affecting their medical care. Participants should inform any member of the study team of their wish to withdraw consent. When a participant withdraws consent, they should be asked whether they are willing to allow ongoing data collection, such as maternal and fetal outcomes, from their medical records. If the participant withdraws consent and does not wish to have any further data collected, then this will be recorded on the database and no further data entry will be possible.

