### Sample size

Prespecified sample size estimation was not carried out given the aim of this observational study was to collate all consecutive eligible case outcomes in participating centres between data collection start and 18 months from start of data collection. It may be useful to provide an approximate guide as to the width of the 95% CI that can be achieved for proportions using historical data from the UK. These historical data may not hold during the current pandemic and may alter due to multiple reasons such as access to healthcare or behaviour changes. Contemporaneous data collected using other current national registries will provide true background rates for comparative purposes at the end of the study period. Generalising these data internationally may not be possible unless similar contemporaneous data exist for comparison.

The estimated representative pre-COVID pandemic incidences of miscarriage, Small for Gestational Age (SGA)/FGR and stillbirth in the UK were 30%, 10%, 0.2%, respectively. The expected outcome proportions during the COVID-19 pandemic are 40%, 15% and 0.4%, respectively. A sample size of 500 would allow the estimation of the width of 95% CIs for the proportion of miscarriage as 40%±4.2%, for SGA/FGR 15%±2.9% and for stillbirth 0.4%±0.3%.

These figures are meant only as a guide and reference proportions may change over this period. Since attaining sufficient precision for stillbirth requires by far the largest sample size, then study recruitment targets could be based on this rarest of outcomes. This would then provide sufficient precision to assess other more common outcomes. These figures are based on data from the UK only. Reference proportions vary by country but are of a similar order to those in the UK.

Appropriate quantitative analyses will be conducted by a study statistician. Dates collected from sites for expected data of delivery or last menstrual period, week of pregnancy at delivery and date of any COVID-19 tests in the participant or neonate will be cross-checked and validated for the final report. Regular interim reports will use contemporaneous data as it is collated.

Derived variables to be reported are:

Infection delivery interval (<2 or≥2 weeks after onset of suspected or confirmed COVID-19).Week of pregnancy when COVID-19 diagnosis was made.Number of days from delivery to SARS-COV-2 testBirth weight percentiles adjusted for gender and gestational age.

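### Three sections give data-collection limits that do not agree, and two of the limits, read literally, can close the registry while registered women are still pregnant

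*Protocol article*

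**What the plan says.** Three sections of the protocol article bear on when data collection ends.

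- Study population: "The study will recruit women affected by suspected COVID-19 or confirmed SARS-CoV-2 infection from January 2020 and March 2021". Women are identified "at the time of an early pregnancy attendance or at delivery".
- Outcomes: "The limit for data collection will be 28 days after the delivery or pregnancy loss of the last woman registered".
- Sample size: no sample size was set, because the aim is to collate all consecutive eligible case outcomes "between data collection start and 18 months from start of data collection".

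The Data entry section collects neonatal events to 28 days, including "readmission up to 28 days of life". The Sample size section places the final analysis at final data collection, so the closure rule also fixes the final data set. The start date of data collection is not given. The nearest calendar clue is in Methods and analysis: "The study received Urgent Public Health (UPH) prioritisation in the UK in April 2020".

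**The concern.** One limit hangs on a single woman's outcome and the other is a fixed calendar span. They would coincide only by chance, and no section says which prevails. The 18 months also does not match the 15-month recruitment window.

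The Outcomes rule is tied to order of registration. Some women enter in early pregnancy and others at delivery, so order of registration is not order of outcome. The last woman registered may deliver the same day, while women registered months before her are still pregnant.

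At stake are the incidences in the principal research question. Women still pregnant at closure are those who entered early and whose pregnancies continue; early losses in the same group are already recorded. Two readings of the closure rule would therefore give two final data sets with different outcome proportions, and the planned 95% CIs would not show the difference.

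**Working it through.** **Inputs.** From the documents: recruitment January 2020 to March 2021; entry in early pregnancy or at delivery; 28 days of follow-up after the outcome; 18 months from an unstated start; expected miscarriage of 40%. Assumed: early entry at 6 weeks, term at 40 weeks for the dates, and data collection starting between April and July 2020.

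**1. Follow-up needed.** A woman registered on 31 March 2021 at 6 weeks has 40 − 6 = 34 weeks to go. She is due on 24 November 2021, and 28 days later is 22 December 2021. Entry at 8, 12 or 20 weeks gives 8 December, 10 November or 15 September 2021.

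**2. The Outcomes rule, read literally.** If the last woman registered enters at delivery on 31 March 2021, data close on 28 April 2021. If she enters at 6 weeks, they close on 22 December 2021. The difference is 238 days (34 weeks). With closure on 28 April 2021, women registered at 6 weeks after about 2 September 2020 would not have reached 40 weeks.

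**3. The 18-month limit.**

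| Assumed start | Closes | Days short of 24 Nov 2021 (due date) | Days short of 22 Dec 2021 (28 days after) |
|---|---|---|---|
| 1 April 2020 | 1 Oct 2021 | 54 | 82 |
| 1 May 2020 | 1 Nov 2021 | 23 | 51 |
| 1 June 2020 | 1 Dec 2021 | none | 21 |
| 1 July 2020 | 1 Jan 2022 | none | none (10 spare) |

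Counting back 18 months, the limit cuts the 28-day follow-up for starts before about 22 June 2020, and the delivery itself for starts before about 24 May 2020.

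**4. Share still pregnant at lock.** Assume infection dates uniform over the 65 weeks from 1 January 2020 to 31 March 2021, gestation at infection uniform over 5-39 weeks, delivery at 39.5 weeks, every woman registered before lock, and a fraction L of those infected before 14 weeks losing the pregnancy before lock. Time to delivery is then uniform over 0.5-34.5 weeks, so the latest delivery falls at week 65 + 34.5 = 99.5.

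For an 18-month lock at week c, and L = 0, the share still pregnant is (99.5 − c)²/2 divided by 65 × 34 = 2210 (all women) or by 65 × 9 = 585 (infected before 14 weeks). All women still pregnant belong to the early group, so a loss fraction L multiplies both shares by 1 − L.

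- April start, c = 91.3: 8.2²/2 = 33.6, giving 1.52% and 5.7%.
- May start, c = 95.7: 3.8²/2 = 7.2, giving 0.33% and 1.2%.

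For the worst literal case of the Outcomes rule, c = 69: 30.5²/2 = 465, giving 21.0% of all. In the early group the mean time to delivery is 30 weeks, so the share is (65 + 30 − 69)/65 = 40%. Here L removes L × 40% × 9/34 from the figure for all women.

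| Lock | L = 0 | L = 12% | L = 40% |
|---|---|---|---|
| 18 months from April 2020 | 1.5% (5.7%) | 1.3% (5.1%) | 0.9% (3.4%) |
| 18 months from May 2020 | 0.3% (1.2%) | 0.3% (1.1%) | 0.2% (0.7%) |
| Outcomes rule, worst case | 21% (40%) | 20% (35%) | 17% (24%) |

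Figures are all women, with early infections in brackets. The 12% is an assumption that appears nowhere in the document; 40% is the document's expected miscarriage proportion, applied here to early infections.

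**5. Effect on a loss proportion.** With completed pregnancies as denominator, the observed proportion is the true one divided by (1 − share still pregnant).

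- Early infections, L = 12%: 12.6% (April start) and 18.5% (Outcomes rule, worst case).
- Early infections, L = 40%: 41.4% and 52.6%.
- Whole cohort, L = 12%: the true proportion is 12% × 9/34 = 3.2%; it reads 3.2% and 4.0%.
- Whole cohort, L = 40%: the true proportion is 10.6%; it reads 10.7% and 12.7%.

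**6. A different case mix.** Suppose 25-75% of women register at 6 weeks and the rest at delivery, registration is uniform from the start to 31 March 2021, and 40% of early registrants miscarry within 1-8 weeks. With T days of registration and closure at day C, the share of early registrants still pregnant is 0.6 × (T + 234.5 − C)/T, where 234.5 days is 33.5 weeks.

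- April: 0.6 × 50.5/364 = 8.3%, or 2.1-6.2% of all women.
- May: 0.6 × 19.5/334 = 3.5%, or 0.9-2.6% of all women.
- Outcomes rule, worst case: by simulation, up to 38% of early registrants and 28.5% of all women.

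**The case against.** The strongest defence is that the sections do different jobs. Only Outcomes uses the language of a limit, and in ordinary registry usage it means following everyone until the last participant is complete. The 18 months sits in a sentence explaining why no sample size was set and may simply describe the study window. Staff are unlikely to stop collecting data while knowing that registered women are still pregnant. This has weight: literal truncation is possible on the words but is not the most natural intention. It does not remove the disagreement, because the 18 months is attached to case outcomes, and as an accrual window it would not match the 15 months of recruitment.

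Stronger readings are tempting, but the document does not support them.

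- A reader might infer that data collection began on 1 January 2020, so that 18 months ends on 1 July 2021, 174 days short of 22 December. January 2020 dates the affected women, not data collection. Prioritisation came in April 2020, and the Introduction was written around literature to 12 May 2020.
- A reader might count as lost every woman whose 28 days are incomplete, about 26% of all and 41% of early infections in the worst literal case. That includes women already delivered, whose miscarriage, stillbirth or preterm status is known.
- A reader might conclude that losses and preterm births will be overstated. That holds only if completed pregnancies form the denominator, which the article does not state and may leave to a fuller document.
- A reader might take the shift among early infections as the shift in the final results. The Sample size section plans outcomes for the whole cohort and by country, and lists no miscarriage proportion by stage of infection.

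**Conclusion.** The disagreement between the three sections is established from the text. Each closure limit, taken as written, can end data collection while registered women are still pregnant: the Outcomes rule because it follows order of registration, and the 18-month limit if data collection started early enough.

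Bias is a possible consequence, not a demonstrated one. With completed pregnancies as denominator, early losses and preterm births are over-represented; with all registered women, late outcomes are under-counted.

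On uniform infection dates and gestations with 12% early loss, an 18-month lock from April or May 2020 leaves about 0.3-1.3% of all women (1-5% of early infections) still pregnant. The worst literal case of the Outcomes rule leaves about 20% (35%). A registry weighted towards early entry would give larger shares, and a later start smaller ones, so these figures indicate order of size only. The point is a should-fix.

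**What to change.** State one rule in Study population, Outcomes and Sample size: each woman is followed to 28 days after her own delivery or pregnancy loss, and data collection closes 28 days after the latest such outcome among all registered women. Give the start date of data collection, and present the 18 months as a planned duration, not as a limit on outcomes.

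If a fixed earlier lock is kept, restrict the final analysis to women whose expected date of delivery plus 28 days precedes it. The expected date is already collected. Selecting on it, and not on whether the pregnancy has ended, keeps or drops losses and continuing pregnancies on the same footing.

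The cost is a wording amendment. The first option moves the lock by a few months at most: about 82 days from an April 2020 start or 51 from a May start, for a 6-week registrant on the last day. The second moves nothing but gives a slightly smaller analysis set.

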### Data collection pathway

The Centre for Trials Research (CTR), Cardiff University, has designed a registry and web portal for data entry for healthcare professionals. The CTR hosts and maintains the study web page (https://pan-covid.org), which allows maternity healthcare providers to register interest in submitting data to an online database. The data manager will manage the registration of healthcare professionals, keeping personal identifiable information on a separate, password protected, spreadsheet with restricted access. The study co-ordinator will manage registration of healthcare professionals and work with the data manager to provide login permission to those who wish to contribute to the register. Login permission will only be granted to healthcare professionals who have confirmed their email address, which must be from a bona fide healthcare or educational organisation and local agreement and ethical approval is in place.

Where a web portal cannot be accessed by the investigators, a bespoke spreadsheet has been designed to allow automatic uploading of data to the main registry database.

### Analysis

Statistical analysis of the data will be carried out a pseudonymised data set containing NHS number (or equivalent international data field). Numerical data for cases reported and outcomes (miscarriage, SGA/FGR, stillbirth, preterm delivery and vertical transmission) will be reported in anonymised, aggregate regular reports, published on the study website.

### Sample size

Prespecified sample size estimation was not carried out given the aim of this observational study was to collate all consecutive eligible case outcomes in participating centres between data collection start and 18 months from start of data collection. It may be useful to provide an approximate guide as to the width of the 95% CI that can be achieved for proportions using historical data from the UK. These historical data may not hold during the current pandemic and may alter due to multiple reasons such as access to healthcare or behaviour changes. Contemporaneous data collected using other current national registries will provide true background rates for comparative purposes at the end of the study period. Generalising these data internationally may not be possible unless similar contemporaneous data exist for comparison.

The estimated representative pre-COVID pandemic incidences of miscarriage, Small for Gestational Age (SGA)/FGR and stillbirth in the UK were 30%, 10%, 0.2%, respectively. The expected outcome proportions during the COVID-19 pandemic are 40%, 15% and 0.4%, respectively. A sample size of 500 would allow the estimation of the width of 95% CIs for the proportion of miscarriage as 40%±4.2%, for SGA/FGR 15%±2.9% and for stillbirth 0.4%±0.3%.

These figures are meant only as a guide and reference proportions may change over this period. Since attaining sufficient precision for stillbirth requires by far the largest sample size, then study recruitment targets could be based on this rarest of outcomes. This would then provide sufficient precision to assess other more common outcomes. These figures are based on data from the UK only. Reference proportions vary by country but are of a similar order to those in the UK.

Appropriate quantitative analyses will be conducted by a study statistician. Dates collected from sites for expected data of delivery or last menstrual period, week of pregnancy at delivery and date of any COVID-19 tests in the participant or neonate will be cross-checked and validated for the final report. Regular interim reports will use contemporaneous data as it is collated.

Derived variables to be reported are:

Infection delivery interval (<2 or≥2 weeks after onset of suspected or confirmed COVID-19).Week of pregnancy when COVID-19 diagnosis was made.Number of days from delivery to SARS-COV-2 testBirth weight percentiles adjusted for gender and gestational age.

Fortnightly bulletins will consist of counts of participants by country, proportions for maternal COVID-19 diagnosis status (suspected, positive test, negative test), week of pregnancy for COVID-19 diagnosis (<23 weeks, 23–36 weeks, ≥37 weeks), weeks of pregnancy at delivery (<23 weeks, 23–36 weeks, ≥37 weeks), maternal and neonatal mortality, outcome of delivery (live birth, miscarriage, intrauterine death, stillbirth (>22+6 weeks gestation)), FGR split by delivery interval (<2 vs ≥2 weeks), COVID-19 diagnosis status for babies split by number of days from delivery to test (0, 1–7, 8–28) and birth weight percentiles. Mean (SD) and median birth weights will also be reported. Further analysis will take place at one interim time point and at final data collection. For the interim analysis, a subset of validated outcomes will be reported consisting of total cohort proportions of gestation at delivery, birth weight Z-scores, perinatal mortality (stillbirth, early neonatal death), neonatal COVID-19 or SARS-COV-2 swab positive, neonatal morbidity and maternal death. These data will be split by suspected and confirmed COVID-19 diagnosis. Additional graphical exploratory analysis of the data will assess any possible association between the infection delivery interval and the timing of delivery as well as birth weight. The final analysis will report all demographic baseline data for the whole cohort and all outcomes as well as these graphical trends. Proportional data for the study outcomes will be presented with 95% CIs, by country, where numbers allow. Data and all appropriate documentation will be stored for a minimum of 10 years after the completion of the study, including the follow-up period.

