**Study registration number:**

ISRCTN68026880.

Strengths and limitations of this studyThe pregnancy and neonatal outcomes in COVID-19 (PAN-COVID) registry aims to collect an international data set, which will enable us to answer a focused set of questions related to pregnancy, maternal and neonatal outcomes of SARS-CoV-2 infection in pregnancy.There is a high likelihood of an adequate sample size to allow us to measure all the stated focused outcomes of SARS-CoV-2 infection in pregnancy.The PAN-COVID protocol facilitates data sharing and collaboration with multiple global partners.This registry establishes a collaborative framework, which can be used to respond effectively to guide care for women in pregnancy and their neonates in future pandemics.Registry studies are generally unlikely to fully capture all cases and therefore carry risk of underestimating infection rates and overestimating infection complication and fatality rates.

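### The confidence-interval half-widths quoted for 500 women do not follow from the stated inputs; the error is small for miscarriage and SGA/FGR but material for stillbirth, where the upper limit is understated about twofold

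*Protocol article*

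**What the plan says.** The Sample size section (Methods and analysis) states that no sample size was prespecified, because the registry takes all consecutive eligible cases at participating centres over 18 months. It then offers "an approximate guide as to the width of the 95% CI that can be achieved for proportions".

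The inputs are explicit. The background rates are given as "pre-COVID pandemic incidences of miscarriage, Small for Gestational Age (SGA)/FGR and stillbirth in the UK were 30%, 10%, 0.2%, respectively". For the pandemic period, "The expected outcome proportions during the COVID-19 pandemic are 40%, 15% and 0.4%, respectively". The guide is worked at one size: "A sample size of 500 would allow the estimation of the width of 95% CIs", with the results "the proportion of miscarriage as 40%±4.2%, for SGA/FGR 15%±2.9% and for stillbirth 0.4%±0.3" percent. No interval method is named.

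The section then singles out the rarest outcome: "Since attaining sufficient precision for stillbirth requires by far the largest sample size", and suggests that recruitment targets could be built on it, since the commoner outcomes would then be estimated well enough. It labels the figures a guide and warns that reference proportions may change.

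**The concern.** A reader who takes the sample size, the proportions and the 95% level from the section and applies the standard formula does not get the printed half-widths. All three are too narrow. For miscarriage and SGA/FGR the gap is a fraction of a point. For stillbirth the printed value is little more than half of what the formula gives.

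Stillbirth is where this matters. It is the outcome the section proposes as a possible basis for recruitment targets, and in a registry looking for excess harm the upper confidence limit shows how large an excess cannot be ruled out. Someone who wants stillbirth estimated to within 0.3 points would conclude from the text that 500 women are enough.

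**Working it through.** **Inputs**, all from the Sample size section: n = 500; p = 40%, 15% and 0.4% (200, 75 and 2 expected events); 95% level, taken as two-sided with z = 1.96. I assume simple binomial sampling with all 500 women in each denominator.

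**Step 1: try to reproduce the printed figures.** Normal-approximation (Wald) half-width = 1.96 × √(p(1 − p)/n):

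- Miscarriage: 1.96 × √(0.40 × 0.60/500) = 4.29 points (printed 4.2)
- SGA/FGR: 1.96 × √(0.15 × 0.85/500) = 3.13 points (printed 2.9)
- Stillbirth: 1.96 × √(0.004 × 0.996/500) = 1.96 × 0.282 = 0.553 points (printed 0.3)

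None reproduces. Other readings, in points:

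| Method at n = 500 | Miscarriage | SGA/FGR | Stillbirth |
|---|---|---|---|
| Printed | 4.2 | 2.9 | 0.3 |
| Wald 95% | 4.29 | 3.13 | 0.55 |
| Wald 95% at pre-pandemic rates | 4.02 | 2.63 | 0.39 |
| Wald 90% | 3.60 | 2.63 | 0.46 |
| One standard error | 2.19 | 1.60 | 0.28 |
| Wilson, half of full width | 4.28 | 3.13 | 0.67 |
| Clopper-Pearson, half of full width | 4.38 | 3.23 | 0.69 |
| Wilson, lower arm only | 4.20 | 2.86 | 0.29 |
| Wilson, upper arm only | 4.36 | 3.40 | 1.05 |

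Of these rows, only the Wilson lower arm (estimate minus lower limit) rounds to all three printed values. The lower arms of the logit interval (4.21, 2.87, 0.30) and the Jeffreys interval (4.23, 2.92, 0.32) do so too. No method tried gives the three values as a symmetric half-width.

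**Step 2: a proper interval for stillbirth.** With 2 expected events the Wald interval is 0.4 ± 0.553, or −0.15% to 0.95%, which runs below zero, so ±0.55 is only a rough correction.

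- Wilson: centre = (p + z²/2n)/(1 + z²/n) = (0.0040 + 0.00384)/1.00768 = 0.778%. Half-width = z√(p(1 − p)/n + z²/4n²)/(1 + z²/n) = 0.668 points. Interval: 0.11% to 1.45%.
- Clopper-Pearson, solving for the rates at which 2 or more, and 2 or fewer, events in 500 each have probability 0.025: 0.05% to 1.44%.

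The printed interval is 0.4 ± 0.3, or 0.1% to 0.7%. Its lower limit is about right. Its upper limit is too low by a factor of 1.44/0.7 ≈ 2.1.

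**Step 3: the size that ±0.3 would need.** n = z²p(1 − p)/d² = 3.8415 × 0.004 × 0.996/0.003² ≈ 1,700. Since 0.3 may be rounded, d = 0.35 gives about 1,250 and d = 0.25 about 2,450. This is a normal-approximation guide. At 1,700 women the Wilson interval around 0.4% is 0.19% to 0.83%, half of whose width is 0.32 points, so the order of magnitude holds.

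**Step 4: what 500 women give.** If the true rate is 0.4%, the estimate falls within ±0.3 points only when 1, 2 or 3 stillbirths occur. That has probability 72%. The chance of no stillbirth at all is 0.996^500 = 13%.

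**The case against.** The strongest defence is that nothing in the design depends on these numbers. The registry enrols every eligible case, sets no sample size, uses 500 as an illustration rather than a target or a cap, and calls the figures a guide. Two of the three discrepancies (0.09 and 0.23 points) would hardly trouble anyone using an approximate guide. This stands, and it limits the consequence. It does not remove the error: the caveat covers uncertainty in the assumed rates, not arithmetic on the rates as stated.

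A second defence is that the figures come from a sound asymmetric method. The Wilson lower arm fits well, but because no method is named this is an inference. Nor does it rescue the text, because a ± sign tells the reader that the upper arm is equally short, and for stillbirth it is 1.05 points.

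Three stronger readings are tempting, and the document does not support them.

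- A reader might infer that the section contradicts itself by saying stillbirth needs the largest sample while printing the smallest half-width. That mixes absolute and relative precision. As printed, 0.3 on 0.4 is a relative half-width of 75%, against about 10% for miscarriage (4.2 on 40), so the statement about stillbirth is right.
- A reader might infer that the text claims 500 women can separate 0.4% from the 0.2% background. It does not: the printed range of 0.1% to 0.7% already contains 0.2%, and the section plans comparison with contemporaneous registry data.
- A reader might infer that the error refutes the bullet under Strengths and limitations, "There is a high likelihood of an adequate sample size to allow us to measure all the stated focused outcomes". That bullet is not tied to 500 women, so an error at 500 does not disprove it.

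**Conclusion.** The point holds as an arithmetic error in the stated precision, material for stillbirth only. On the section's own inputs the half-widths are about 4.3 and 3.1 points for miscarriage and SGA/FGR, against 4.2 and 2.9 printed. For stillbirth the Wald half-width is 0.55 rather than 0.3, and the suitable interval is asymmetric: 0.05% to 1.44% exact, or 0.11% to 1.45% Wilson. The printed upper limit of 0.7% is about half the correct value.

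This rests on two-sided 95% intervals, binomial sampling and the stated 500 women and proportions; it does not depend on how the figures arose. It should be corrected because these are the article's only precision figures and the worst affected is the one proposed for setting recruitment targets. It does not show that the registry is too small, since no size was fixed.

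**What to change.** In the Sample size section, replace the three intervals with: miscarriage 40% (about ±4.3 points), SGA/FGR 15% (about ±3.1 points), and stillbirth 0.4% with exact 95% interval 0.05% to 1.44%, based on 2 expected events. Name the method used for each. Add that 500 women do not estimate stillbirth to within 0.3 points, and that a half-width near 0.3 would need roughly 1,700 women by the normal approximation (about 1,250 to 2,450 allowing for rounding of 0.3).

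The cost is a text correction with less favourable figures. No change to design, eligibility, data collection or recruitment follows from it.
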